## Methods

### Participants

All military members with a new medical referral for physiotherapy services at the Valcartier Health Centre for either low back pain, patellofemoral pain syndrome, rotator cuff-related shoulder pain or lateral ankle sprain and who agree to participate in the study will be consecutively recruited. A PT will evaluate all potential participants to confirm their eligibility. To be eligible, military members will have to be aged between 18 and 60 years and present one of the four targeted MKSd:

Low back pain: Inclusion – 1) LBP with or without radiation to the lower limbs, 2) minimal score of 17% on the Modified Oswestry Disability Index (ODI) (based on its clinically important difference [CID] [23]). Exclusion – 1) history of surgery or facture to the spinal column, 2) signs of upper motor neuron lesions (bilateral paresthesia, hyperreflexia or spasticity) [24] or other redflags (e.g. fracture) [25].

Patellofemoral pain syndrome: Inclusion – 1) anterior knee pain during running or during at least two activities among: kneeling, squatting, and resisted knee extension [26], 2) score lower than 85/100 on the Knee Outcomes Survey – Activity of Daily Living Scale (KOS-ADLS) [27]. Exclusion – 1) history of knee surgery or patellar dislocation; 2) pain believed to originate either from meniscus (presence of joint line fullness and tenderness, McMurray sign, and positive Thessaly test) [28] or from any knee ligament.

Rotator cuff-related shoulder pain: Inclusion – 1) at least one positive finding in each of the following categories: a) painful arc of movement; b) positive Neer’s or Kennedy-Hawkins Test; c) pain on resisted external rotation, resisted abduction or Empty Can Test [29], 2) minimal score of 14 points on the *Quick*DASH [30]. Exclusion – 1) history of shoulder surgery, fracture, capsulitis, or dislocation, 2) full thickness rotator cuff tear identified by imagery or clinical tests [31], 3) cervicobrachialgia or shoulder pain reproduced by neck movements.

Lateral ankle sprain: Inclusion – 1) unilateral lateral ankle sprain of < 6 weeks, 2) minimal score of 9 points on the LEFS [32]. Exclusion – 1) ankle fracture, 2) lateral ligaments not the principal injury (a high ankle/tibiofibular sprain).

For all four MSKd, potential participants will be excluded if they 1) are unavailable to participate in a 12-week intervention; 2) have a diagnosis of rheumatoid, inflammatory, neurological or neurodegenerative disease; 3) received a corticosteroid injection in the previous 6 weeks in the affected region; or 4) have had more than 6 months of work restriction for their current MSKd [20]. Furthermore, patients admitted to the physiotherapy clinic of the Valcartier Health Centre with an acute condition and who present constant and intense pain (> 5/10), severely limited range of motion (more than 50% in at least 2 directions) [20], obvious lateral shift for LPB or unable to bear weight (for lateral ankle sprain) will first be treated one-on-one by a PT and then be referred to the research team once the condition is no longer acute, based on the same criteria. Acute conditions that require one-on-one follow-up initially will be documented.

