### Outcomes

The primary outcome will be functional limitations, as measured with the Pain Interference subscale of the Brief Pain Inventory – Short Form (BPI). The secondary outcomes will include pain severity as measured with the Pain Severity subscale of the BPI, and health-related quality of life as measured with the EQ-5D-5L. As pain-related fear has been shown to influence outcomes in military members and conservative management reduces pain-related fears [20, 46], both interventions will also be compared on their impact on pain-related fears, measured with the Tampa Scale for Kinesiophobia (TSK) [38]. Furthermore, region-specific symptoms and functional limitations will be assessed using the Oswestry Disability Index (ODI) for low back pain, the shortened version of the Disabilities of the Arm, Shoulder and Hand (*Quick*DASH) for rotator cuff-related shoulder pain, Knee Outcome Survey Activities of Daily Living Scale (KOS-ADLS) for patellofemoral pain syndrome and Lower Extremity Functional Scale (LEFS) for lateral ankle sprain. To monitor compliance with home exercises, participants will be asked to maintain a weekly web-based logbook on RedCap during the 12 weeks of the intervention. Finally, participant’s satisfaction with treatment will be assessed at the end of the treatment (i.e., week-12) (see bellow for further description).

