### Region-specific symptoms and functional limitations

#### For low back pain

The modified ODI is a 10-item questionnaire that assesses the interference of low back pain with activities of daily living. Its reliability (MDC = 10 points), construct validity and responsiveness to change (CID ranges from 10 to 14) have been demonstrated [23, 54–57].

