#### For lateral ankle sprain

The LEFS is a 20-item questionnaire assessing the impairment of the lower-extremity MSK system in everyday activities [60]. It has been validated in individuals with lateral ankle sprain, and its reliability, construct validity and responsiveness have all been demonstrated (MDC and CID are both 6 points) [61].

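### The LEFS entry criterion for lateral ankle sprain is written as a floor; if a higher score means better function, it admits full function and screens out only the most limited

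*Protocol article*

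**What the plan says.** Under Participants, each of the four conditions carries a score criterion next to its clinical criteria:

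- Low back pain: at least 17% on the modified ODI.
- Rotator cuff-related shoulder pain: at least 14 points on the QuickDASH.
- Patellofemoral pain: "score lower than 85/100 on the Knee Outcomes Survey" (the KOS-ADLS).
- Lateral ankle sprain: "minimal score of 9 points on the LEFS".

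The Outcomes section lists the "Lower Extremity Functional Scale (LEFS) for lateral ankle sprain". The instrument section for lateral ankle sprain says: "The LEFS is a 20-item questionnaire assessing the impairment of the lower-extremity MSK system in everyday activities". It adds that the "MDC and CID are both 6 points". The article gives no item range, no total range and no scoring direction for the LEFS, and Participants gives no basis for the figure 9 beyond a citation.

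**The concern.** A score criterion of this kind should make sure that entrants have enough limitation for improvement to be measurable. On a scale where high means worse, that calls for a floor. On a scale where high means better, it calls for a ceiling. The article follows this logic for the ODI, the QuickDASH and the KOS-ADLS. The LEFS is named a functional scale but has a floor.

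If the name describes the scoring, a screening form that applies the sentence literally would accept ankle patients at full LEFS function and turn away only those with the lowest scores. Three things would be at stake:

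- The LEFS is the region-specific outcome for this stratum in the exploratory analyses, so entrants at its ceiling have no room to improve on it.
- The Interventions section ends supervised treatment once symptoms or functional limitations are gone. A person at full LEFS function at entry could already be near the functional part of that condition.
- The Sample size section says the numbers allow effects to be determined for each condition, which presupposes entrants who are limited in each.

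**Working it through.** **Size of the stratum.** The article plans 15 participants per diagnosis per group. Two groups give 15 × 2 = 30 ankle participants, and 30/120 = 25% of the sample. The sample size uses BPI Pain Interference figures only; the LEFS does not enter it, so the planned number is unaffected.

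**Which scores the rule admits.** The plan gives no figure to reproduce here, so the check is an enumeration. Let the LEFS total run over the integers 0 to M. The article does not give M, so it is varied as an assumption (20 items, item maximum 1 to 5). A floor of 9 admits M − 8 of the M + 1 possible scores.

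| Assumed M | Scores admitted by a floor of 9 | Share of possible scores | Upper bound if 9 is a deficit (M − 9) |
|---|---|---|---|
| 20 | 12 of 21 | 57% | 11 |
| 40 | 32 of 41 | 78% | 31 |
| 60 | 52 of 61 | 85% | 51 |
| 80 | 72 of 81 | 89% | 71 |
| 100 | 92 of 101 | 91% | 91 |

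These are shares of possible scores, not of patients.

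- If higher means better, the admitted set contains the best score for every M of 9 or more, and the excluded set is 0 to 8, the worst scores. The maximum does not matter to this result.
- If higher means worse, the excluded set 0 to 8 is the least limited, and the rule works as intended.

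The result therefore turns on scoring direction alone.

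**What the article implies about direction.** The name points to higher meaning better. The description speaks of impairment, which could point the other way. But the KOS-ADLS is described as evaluating symptoms and functional limitations, and there it is the low scores that qualify. The descriptive wording does not settle direction for either scale.

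**What the figure 9 was probably meant to be.** Set each cut-off, expressed as a deficit from no limitation, beside the CID in the matching instrument section:

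| Scale | Required deficit | Quoted CID |
|---|---|---|
| ODI | 17 | 10 to 14 |
| QuickDASH | 14 | 10 |
| KOS-ADLS | 100 − 85 = 15 | 13.6 |
| LEFS | 9, if read as a deficit | 6 |

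Each of the first three requires a deficit somewhat above the CID, so that a clinically important improvement is possible. Nine against 6 fits the same pattern, but only as a distance from full function. This supports reading 9 as a deficit. It does not by itself prove direction: on a scale where high means worse, a raw score of 9 already is that deficit. Together with the scale's name, it suggests that a deficit was written as a raw score.

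**The case against.** The strongest objection is that the reversal is not demonstrated. The article never states the LEFS direction or range, and under the opposite direction the sentence is correct as it stands. That objection stands as a condition on the finding. It does not remove it: the name, the contrast with the KOS-ADLS and the pattern of the other cut-offs all favour a reversed wording, and a reader cannot apply the criterion safely without knowing the direction.

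It can also be said that the practical reach is limited. Entrants need a new medical referral for physiotherapy and a sprain of under 6 weeks, with eligibility confirmed by a physiotherapist, so few may be at full function. Acute patients who cannot bear weight, or who have severe pain or loss of motion, are treated one-on-one first, so few may score 0 to 8 when they reach the research team. Both points are fair, and both limit the likely harm.

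A reader might also infer three stronger things that the article does not support:

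- **That 9 against a CID of 6, or 17% against an ODI statement that the "CID ranges from 10 to 14", is an error.** Nothing says that 9 is the LEFS CID. The ODI cut-off is said to be based on a CID, not to equal it. An entry deficit above the CID is reasonable and is the pattern across all four scales.
- **That the arm difference would shrink by a calculable amount.** No figure in the article gives the share of ankle entrants at the LEFS ceiling. Nor does a person at that ceiling necessarily have no pain interference on the BPI, so LEFS dilution cannot be carried over to the primary outcome.
- **That the correct limit can be read off.** It depends on a maximum that the article does not give; across the maxima tried above it runs from 11 to 91.

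**Conclusion.** The concern holds in a limited form. On the assumption that a higher LEFS score means better function, the ankle criterion as written selects the wrong end of the scale, and 30 of 120 participants (25%) have no working score criterion for minimum limitation. They are not without any filter, since the referral and diagnostic criteria remain, so what is admitted is a person with no limitation on the LEFS, not a person with no injury.

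The direct exposure is the exploratory LEFS analysis in the ankle stratum. The effect on BPI Pain Interference is indirect and of unknown size. A reader might go on to infer that the trial is materially tilted towards finding the group programme at least as effective; the article gives no basis for sizing such a tilt or for showing that it occurs. If the LEFS is in fact scored with higher meaning worse, the criterion stands and only the missing statement of direction remains. This is a wording correction worth making before the rule is applied, not a threat to the sample size or the primary analysis.

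**What to change.** 1. State the range and scoring direction of the LEFS, in Participants or in its instrument section.
2. If higher means better function, reword the ankle criterion as an upper bound: a score at least the intended deficit below the maximum. The investigators should confirm whether 9 is that deficit; no threshold is proposed here.
3. Check that the screening form, and any screening already done, applies the criterion in the intended direction.

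The cost is one line of eligibility text and one check of the screening form. The sample size, randomisation and analysis need no change.

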### Sample size

Based on our sample size calculation, calculated for our primary outcome (Pain Interference subscale of the Brief Pain Inventory) using data from a pilot study on military members with MSKd [33], 15 participants per diagnosis will be required per group for a total of 120 participants (60 participants/group) (G*Power 3.1.7; α = 0.05, 1-β = 0.95, Baseline mean: 2.9+/− 1.5 points, Follow-up mean: 0.8+/− 1.2 points, expected lost at follow-up = 15% [based on past experiences with this population]. This number will enable us to determine the effects of the interventions for each of the four conditions.

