### Statistical analyses

Descriptive statistics will be used for all outcome variables at each measurement time to summarise results. Baseline demographic data will be compared (independent *t*-tests and Chi-squared tests) to establish the comparability of groups. An intention-to-treat analysis will be used in which all participants will be analysed in the group to which they were assigned. In addition, sensitivity analyses will also be performed using per-protocol analyses; these analyses will allow to verify the consistency of the results in participants strongly compliant with the interventions (e.g., 75% attendance and home exercises). All dropouts and the reason for dropping out of the study will be reported. Any harm or unintended effects and co-interventions will be recorded. A 2-way ANOVA (2 Interventions [Group-Based or UPC] × 4 Times [0, 6, 12, 26 weeks]) will be used to analyse and compare the effects of the interventions on the primary outcome (Pain Interference Scale) and on four of the secondary outcomes (Pain intensity subscale, EQ-5D-5L, TSK) (SPSS, proc. GENLIN [Generalized Estimating Equations – GEEs]). Effect sizes (Cohen’s *d* for between-groups comparisons, Glass’s Δ for within-group comparisons) will be calculated. Nonparametric Analysis for Longitudinal Data (nparLD Package 2.1, R-software, v.3.6.1) will also be considered in cases where GEEs are not applicable (undefined distributions). If nparLD are used, effect sizes will be reported as relative treatment effect. Satisfaction with treatment will be compared between the two interventions using Chi-squared test for the PASS and Mann Whitney test or independent *t*-tests for satisfaction questions using the Likert scales. Exploratory analyses (using a similar statistical approach as for primary outcome) will be performed to compare the two interventions for each of the four conditions using the region-specific questionnaires (ODI, KOS-ADLS, *Quick*DASH, LEFS).

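### The 95% power was computed for the pilot's change over time, not for a difference between arms, and the per-condition claim built on it conflicts with the analysis section

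*Protocol article*

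**What the plan says.** The Sample size section states that "15 participants per diagnosis will be required per group for a total of 120 participants (60 participants/group"). The inputs, obtained "using data from a pilot study on military members with MSKd", are "α = 0.05, 1-β = 0.95", "Baseline mean: 2.9+/− 1.5 points", "Follow-up mean: 0.8+/− 1.2 points" and "expected lost at follow-up = 15" per cent. The outcome is the BPI Pain Interference subscale. The section gives no between-arm difference and no margin. It ends: "This number will enable us to determine the effects of the interventions for each of the four conditions".

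The Background section sets a between-arm objective (group programmes against usual individual physiotherapy) and hypothesises that the group programmes do no worse. The Statistical analyses section tests the primary outcome in a model of two interventions by four times, not split by condition. For single conditions, it says that exploratory analyses "will be performed to compare the two interventions for each of the four conditions using the region-specific questionnaires" (ODI, KOS-ADLS, QuickDASH, LEFS).

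**The concern.** A sample size for a randomised comparison needs the difference between arms, or the margin, that the trial should be able to detect or exclude. The only effect supplied here is how much pilot participants improved from baseline to follow-up. Both arms of this trial receive supervised exercise-based care and a home programme, so both can be expected to improve, and the difference between them should be much smaller than the improvement in either.

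Two things are at stake. First, a reader will take 95% power as a property of the between-arm test, and nothing in the section supports that. Second, the closing sentence invites readers to treat a non-significant result in one condition as an answer for that condition, although modest differences there would usually be missed.

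**Working it through.** **Inputs from the Sample size section.** Baseline 2.9 (SD 1.5); follow-up 0.8 (SD 1.2); alpha 0.05; power 0.95; loss 15%; 15 per diagnosis per arm. The section does not say whether the test is one- or two-sided; two-sided is assumed.

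**Step 1. Reproduce the plan's figure.** Treat baseline and follow-up as two independent groups.
- Difference: 2.9 − 0.8 = 2.1.
- Pooled SD: √[(1.5² + 1.2²)/2] = √1.845 = 1.358.
- Standardised effect: d = 2.1/1.358 = 1.546.
- Two-sample t-test (noncentral t): n = 11 per group gives 93.1% power and n = 12 gives 95.1%, so 12 are needed.
- Loss: 12/0.85 = 14.1, rounded up to 15.
- Total: 15 × 4 conditions × 2 arms = 120.

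This matches exactly, but it does not prove which software option was used. A one-sided two-sample test with SD 1.5 also gives 12, hence 15. So does a paired test if the baseline-to-follow-up correlation is about 0.1; correlations of 0, 0.3, 0.5 and 0.7 give 16, 12, 10 and 8. All these routes use the same 2.1-point change over time, which is all that the argument needs.

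**Step 2. What that implies between arms.** A 2.1-point gap equals the pilot's whole improvement. If one arm improves as in the pilot, the other would have to stay at baseline.

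**Step 3. Power for a real between-arm contrast.** The documents give no between-arm difference, so differences of 0.5 to 1.5 points are assumed for illustration. The SD is taken as 1.2 (pilot follow-up) to 1.5 (pilot baseline). The test is an unadjusted, two-sided two-sample t-test at one time point.

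Evaluable per arm: 15 × 0.85 = 12.75 per condition; 60 × 0.85 = 51 pooled.

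| | SD 1.2 | SD 1.5 |
|---|---|---|
| Per condition: detectable at 80% / 95% power | 1.39 / 1.79 | 1.74 / 2.24 |
| Per condition: power for 0.5 points | 17% | 13% |
| Per condition: power for 0.8 points | 37% | 25% |
| Per condition: power for 1.0 point | 52% | 37% |
| Per condition: power for 1.5 points | 86% | 68% |
| Pooled: detectable at 80% / 95% power | 0.67 / 0.86 | 0.84 / 1.08 |
| Pooled: power for 0.5 points | 55% | 39% |
| Pooled: power for 1.0 point | 99% | 92% |

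**Step 4. Precision.** The 95% CI half-width is t × SD × √(2/n).
- Pooled, n = 51, t = 1.984: 0.47 (SD 1.2) to 0.59 (SD 1.5).
- Per condition, n = 12.75, t = 2.066: 0.98 to 1.23.

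**Step 5. The per-condition sentence against the analysis section.** The sample-size claim follows from a calculation on BPI Pain Interference. The planned per-condition comparisons are labelled exploratory and use four region-specific questionnaires, for which the section gives no sizing inputs.

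**The case against.** **The plan's arithmetic is right.** It is, and the stated number reproduces. The fault lies in the choice of effect, not in the calculation.

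**The effects of the interventions could mean change within each arm.** The wording allows this, and 15 per cell would support it. But the 95% power would then say nothing about the randomised comparison, and the Statistical analyses section plans to compare the two interventions within each condition.

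**The per-condition analyses are already called exploratory.** That softens the point. What remains is a conflict of wording between the two sections.

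**The planned model is longitudinal, so an unadjusted t-test is pessimistic.** This stands as a limit on the figures above; the plan gives no correlation. As an illustration, adjusting for a baseline correlation of 0.5 to 0.7 multiplies the SD by √(1 − r²). At SD 1.2, per-condition power for 1.0 point then rises from 52% to 64–81%, but for 0.5 points it reaches only 21–29%.

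Three stronger readings are tempting and should not be drawn:
- A reader might infer that the whole trial is underpowered. The pooled comparison has 92 to 99% power for 1 point, so the documents do not show this.
- A reader might infer that per-condition tests will nearly always be non-significant whatever the truth. Power of 68 to 86% for 1.5 points contradicts that.
- A reader might infer that, because the pilot follow-up mean is 0.8 on a scale that stops at 0, no per-condition difference above 0.8 is possible. That assumes usual care reaches 0.8, which the plan does not say. It also limits only superiority of the group arm, whereas the hypothesis is mainly about that arm not being worse.

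**Conclusion.** The justification is wrong as written. The stated 95% power rests on a 2.1-point change over time (d = 1.546) and carries over to the between-arm comparison only for a gap of about that size, which is implausible for two active treatments under a hypothesis of no less benefit. For a single condition, the detectable difference is 1.39 to 1.74 points at 80% power and 1.79 to 2.24 at 95%. The pooled detectable differences are 0.67 to 0.84 and 0.86 to 1.08.

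These figures assume an SD of 1.2 to 1.5, 15% loss and a two-sided unadjusted t-test. Baseline or repeated-measures adjustment would improve them by an amount that the plan does not allow one to compute. The conclusion concerns the stated basis and the per-condition claim; it is not a finding that 120 participants are too few. The conflict with the exploratory status of the per-condition analyses stands independently of the power figures.

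**What to change.** Keep 120 participants and make two changes to the Sample size section.

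1. Replace the 95% power justification with a pooled between-arm statement. For example: 51 evaluable participants per arm give 80% power to detect a difference of 0.67 points at SD 1.2 or 0.84 at SD 1.5, or 95% power for 0.86 or 1.08, with a 95% CI half-width of about 0.47 to 0.59. If a non-inferiority margin is used, justify it on clinical grounds; do not read it off these figures.
2. Delete the sentence about each of the four conditions, or reword it to say that condition-specific results are exploratory and that, on the BPI, they would be estimated with a 95% CI half-width of about 1.0 to 1.2 points.

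A treatment-by-condition interaction on the BPI, which all four conditions share, could be added, but it is optional and would itself have low power.

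The cost is rewording one paragraph, with no extra participants. The downside is that the stated power becomes less favourable.
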